## Abstract

**Background:**

Low back pain (LBP) is a leading cause of disability and healthcare utilization worldwide, yet management in primary care often remains inconsistent with clinical guidelines, with underuse of high-value care and persistent use of low-value interventions. The primary objective of this study is to evaluate the effectiveness of PRIME (PRImary care MultilEvel intervention for low back pain) compared with usual care in terms of cost-effectiveness (system level), back-related imaging rates (practitioner level), and self-reported disability (patient level), while concurrently examining implementation processes.

**Methods:**

This study uses an effectiveness–implementation hybrid type 1 design (NCT07137065). Effectiveness will be evaluated through a pragmatic cluster randomized controlled superiority trial conducted in primary care in Switzerland, recruiting 500 patients with LBP from February 2026 to June 2027. General practitioner quality circles will be randomized to PRIME or usual care. PRIME combines clinician training, patient education resources, automated decision support, and a stepped care pathway aligned with patients’ risk of chronicity. Implementation outcomes and determinants will be assessed in the intervention group using quantitative and qualitative methods guided by established implementation frameworks.

**Discussion:**

This trial will provide a comprehensive evaluation of a multilevel intervention targeting both clinical and implementation gaps in LBP care. By integrating effectiveness and implementation outcomes, the study aims to generate actionable evidence on how high-value LBP care can be sustainably implemented in routine primary care and inform future scale-up strategies.

## Introduction

1

Low back pain (LBP) is the leading cause of disability worldwide and represents a substantial burden for healthcare systems, particularly in primary care settings [1]. In Switzerland, 50% of people report recurrent LBP, which is associated with work limitations, and increased healthcare utilization [2]. Despite well-established clinical guidelines [[3], [4], [5]], the management of LBP in primary care remains highly variable, with underuse of high-value care, and overuse of low-value care strategies [6,7]. Therefore, effective strategies are needed to improve the integration of guideline-concordant care in primary care [8].

Unhelpful beliefs about LBP, such as thinking that the back is fragile and that LBP is caused by serious injury, are frequently identified among healthcare professionals [9,10], patients with LBP [11] and the general population [12,13]. These beliefs are associated with maladaptive behaviors and reduced use of high-value care [14,15]. They are also associated, together with other psychological factors, with an increased risk of chronic disabling LBP [16]. Moreover, clinicians report limited confidence and lack of practical tools to identify and address these psychological risk factors in daily practice [17,18]. Interventions that support clinicians to address these factors early and to align care with patients’ risk of chronicity may improve recovery and reduce unnecessary investigations and costs [19,20].

Supporting clinicians to integrate best practice recommendations requires more than education alone. Multilevel, theory-informed interventions co-designed with stakeholders, adapted to local contexts, and supported by implementation strategies such as reminders, decision-support tools, audit and feedback are more likely to lead to sustainable behavior change [[21], [22], [23], [24]]. Effectiveness–implementation hybrid designs have been recommended to simultaneously evaluate clinical effectiveness and implementation processes, while optimizing research efficiency [[25], [26], [27]].

The PRImary care MultilEvel intervention for low back pain (PRIME Back Study) was co-developed by clinicians, LBP experts and people with lived experience of LBP to improve the integration of high-value care in primary care through a coordinated, multilevel strategy. The intervention was designed to help general practitioners (GPs) and physiotherapists to address psychological risk factors of chronicity, reduce low-value care and increase high-value care strategies.

The primary objective of this effectiveness-implementation hybrid trial is to evaluate the effectiveness of PRIME compared with usual care at three levels: cost-effectiveness (system-level); imaging prescription rate (practitioner-level), and self-reported back-related disability (patient-level). These three distinct, complementary primary outcomes will facilitate a rigorous evaluation to ascertain whether it is advisable to implement the PRIME intervention. Cost-effectiveness was selected as the system-level primary outcome because demonstrating value for money is essential for health policy decisions in LBP care [28]. The imaging prescription rate was selected as the practitioner-level primary outcome because it is a direct, objective indicator of guideline-concordant GP behavior and a key target of PRIME's clinician-facing components [29]. Self-reported back-related disability was selected as the patient-level primary outcome because it is recommended as a core outcome in LBP research [30]. Usual care in this trial reflects standard primary care practice in a healthcare network in French-speaking Switzerland, where GPs already participate in regular quality circle meetings and have unrestricted access to specialist referral, physiotherapy, and interdisciplinary rehabilitation. This high-quality, ecologically valid comparator was chosen to demonstrate the added value of PRIME over existing care. Secondary objectives include evaluating the effectiveness of PRIME on opioid and sick leave prescriptions, clinicians' beliefs and confidence in treating patients with LBP (practitioner-level), as well as pain intensity, work participation, health-related quality of life, global perceived change, pain self-efficacy, fear avoidance beliefs, and beliefs about LBP (patient-level). In addition, implementation processes and outcomes will be examined among healthcare practitioners, including acceptability, appropriateness, feasibility, adoption, fidelity, and barriers and facilitators to implementation. Finally, patients' experience and acceptability of PRIME will be investigated qualitatively.

## Methods

2

### Trial context and design

2.1

This study employs an effectiveness-implementation hybrid type 1 design, in which clinical effectiveness is the primary focus while implementation processes are evaluated as secondary objectives [[25], [26], [27]]. Effectiveness will be evaluated through a pragmatic, cluster-randomized controlled superiority trial comparing PRIME with usual care at system, practitioner and patient levels. The 20 quality circles (clusters) will be randomly allocated to the intervention or control group at a 1:1 ratio (10 intervention clusters, 10 control clusters). All clusters are drawn from a single healthcare network (“Réseau Delta”) in French-speaking Switzerland. Within this network, GPs take part in regular quality circles—small groups of about five to ten physicians—that offer a structured setting for peer exchange and continuous practice improvement. Implementation processes will be investigated using quantitative and qualitative methods [25,26].

This study was approved by the Regional Ethic Committee (CER-VD, 2025-01380). Healthcare practitioners participating in the study and all patients signed an informed consent. The study is registered on clinicaltrials.gov (NCT07137065). Patient recruitment is planned from February 2026 to June 2027.

### Patient and public involvement

2.2

One person living with LBP is a member of the core research team and contributed to the development of the intervention and study design, including selection of outcome measures, educational materials, and study procedures. He will also participate in data interpretation and dissemination.

### Eligibility criteria

2.3

#### Healthcare professionals

2.3.1

Clusters will consist of quality circles of general practitioners (GPs) from the Réseau Delta. Quality circles will be eligible if their GPs practices are located within 20 min by car or 30 min by public transport from an interdisciplinary management clinic. GPs will be eligible if they belong to an included quality circle, provide informed consent, and complete the pre-study training (2 h for the intervention group; 30 min for the control group). To minimize contamination, if GPs from the same practice belong to two different quality circles, only those belonging to one of these circles will be eligible. Physiotherapists will be eligible if they complete the two-day PRIME training and have facilities for active therapy. Occupational therapists will be eligible if they work in an interdisciplinary management clinic participating in the study. Health professionals are eligible to take part irrespective of their level of clinical experience.

#### Patients

2.3.2

Patients aged ≥18 years consulting a participating GP for a primary complaint of LBP (with or without leg pain) will be eligible. There is no upper limit on LBP duration, reflecting the heterogeneity of LBP presentations in primary care. Pain duration at baseline will be recorded. Exclusion criteria include consultation with their GPs for LBP within the previous three months; inability to provide informed consent; inability to access or complete French-language electronic questionnaires; pregnancy; lumbar surgery within the past six months; or confirmed specific spinal pathology (e.g. inflammatory disease, malignancy, infection, fracture, or cauda equina syndrome). Patients will also be excluded if they present with a major motor deficit defined as grade ≤ 3 on the Medical Research Council Scale for muscle strength, indicating movement possible against gravity but not against resistance, or if they require immediate referral to emergency or specialist care [31]. As specific causes of LBP may not be identifiable at initial consultation, patients with a subsequent confirmed diagnosis of specific spinal pathology may be excluded post allocation. The rate of post-randomization exclusion due to confirmed specific spinal pathology is expected to be approximately 1–3% of enrolled patients and is not anticipated to differ systematically between study groups [19]. All post-randomization exclusions will be performed by a blinded medical doctor and reported in the CONSORT flow diagram.

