### Outcomes

2.6

The primary system-level outcome is the incremental cost per quality-adjusted life-year (QALY), estimated using the EQ-5D-5L, incorporating costs from both a healthcare payer and a societal perspective [43]. Direct medical costs over 12 months will be collected through a structured patient-reported healthcare utilization questionnaire administered at each follow-up time point, capturing GP consultations, physiotherapy, specialist visits, investigations (imaging, blood tests), medications, injections, surgery, and hospitalization, previously used in Switzerland [28]. Where available, self-reported data will be complemented and validated using health insurance reimbursement data provided by the main healthcare insurances in Switzerland, covering patients insured by this provider. Indirect costs related to absenteeism and presenteeism will be assessed using the Work Productivity and Activity Impairment Questionnaire (WPAI) [44,45].

The primary practitioner-level outcome is the proportion of patients receiving back-related imaging within 6 months of the initial consultation [29,35]. Secondary practitioner-level outcomes include opioid prescription, medication use, imaging rates and total number over 12 months, clinicians’ beliefs about LBP (measured with the 10-item Back Pain Attitudes Questionnaires, Back-PAQ), and confidence in managing LBP [[46], [47], [48], [49]].

The primary patient-level outcome is back-related disability measured by the 24-item Roland–Morris Disability Questionnaire (RMDQ) at 6 months [50]. Secondary patient-level outcome measures include pain intensity (Numerical Rating Scale, NRS), health-related quality of life (EQ-5D-5L), work participation (WPAI), Global Rating of Change (11-point scale, GRC), pain self-efficacy (Pain Self-Efficacy Questionnaire short form, PSEQ-2), a range of psychological factors, including Fear of movement, Catastrophizing, Anxiety, Depression (Brief screening questions from Kent et al., 2014, BSQ), expectations to return to work (one question from Orebro questionnaire), beliefs about LBP (10-item Back-PAQ) and reassurance (Reassurance Questionnaire) [43,46,[51], [52], [53], [54]]. Based on the advice of our patient partner, two questions were added about capacity to perform valued activities and confidence in their back. PSEQ-2, BSQ and Back-PAQ questionnaires will help investigate the mechanisms of action of the PRIME intervention.

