### Statistical methods

2.12

Cost-effectiveness will be evaluated as the incremental cost-effectiveness ratio (ICER), expressed as net cost in CHF per quality-adjusted life-year (QALY) gained. QALYs will be derived from the EQ-5D-5L assessed at baseline and at 3, 6, and 12 months, using the French EQ-5D-5L value set [66], as there is currently no value set for Switzerland. QALYs will be estimated using the area-under-the-curve method over the 12-month follow-up, meaning that QALYs are calculated by multiplying the patients’ health state utility scores with the time spent in that health state.

Costs from the healthcare payer perspective will be estimated from self-reported healthcare utilization and, where available, health insurance data, applying current Swiss tariffs (TARDOC). The societal perspective will additionally include productivity losses due to absenteeism and presenteeism, assessed using the WPAI. Costs and QALYs will not be discounted given the one-year time horizon. Uncertainty will be assessed using non-parametric bootstrapping to estimate 95% confidence intervals for the ICER, and probabilistic sensitivity analyses will be conducted [67,68]. Cost-effectiveness will be explored across a range of willingness-to-pay thresholds.

Practitioner and patient-level outcomes will be analyzed according to the intention-to-treat principle by a blinded statistician. Primary and secondary continuous outcomes will be analyzed using linear mixed-effects models with random intercepts for clusters to account for the hierarchical structure of the data (patients nested within quality circles). Adjusted models will also be performed based on baseline variables (e.g. age, gender, socio-economic health determinants, RMDQ). Categorical outcomes (e.g. imaging prescription) will be analyzed using generalized linear mixed models [69].

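### Exclusion after allocation for later-confirmed spinal pathology depends on a diagnosis that PRIME could influence, and conflicts with the intention-to-treat statements

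*Protocol article*

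**What the plan says.** Under Eligibility criteria, Patients (2.3.2), the protocol article notes that a specific cause may not be recognisable at the first visit, and so "patients with a subsequent confirmed diagnosis of specific spinal pathology may be excluded post allocation". The rate is "expected to be approximately 1–3% of enrolled patients and is not anticipated to differ systematically between study groups". The safeguard is this: "All post-randomization exclusions will be performed by a blinded medical doctor and reported in the CONSORT flow diagram". The Blinding section (2.10) repeats that a blinded doctor decides on exclusions. The article sets no time limit, does not require that the pathology was present at the index visit, and does not say that excluded patients stay in any analysis.

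Statistical methods (2.12) states: "Practitioner and patient-level outcomes will be analyzed according to the intention-to-treat principle". It later adds that patients are analysed by the cluster allocation at enrolment.

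The Introduction describes the imaging rate as a "direct, objective indicator of guideline-concordant GP behavior and a key target of" PRIME's clinician-facing components. The practitioner-level primary outcome is the "proportion of patients receiving back-related imaging within 6 months of the initial consultation". Direct costs, part of the system-level primary outcome, include "specialist visits, investigations (imaging, blood tests), medications, injections, surgery, and hospitalization". Table 1 lists, among the GP components of PRIME, ruling out infection, osteoporotic fracture and severe neurological problems at the first consultation.

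**The concern.** Excluding randomized patients is harmless only if the trigger cannot be affected by allocation. Here the trigger is a diagnosis confirmed during follow-up. PRIME is designed to change how often GPs order imaging and how they assess patients at the first visit, and both can change whether and when a specific cause is confirmed. Control GPs keep unrestricted imaging and specialist referral (2.5.2). The expectation that exclusion "is not anticipated to differ systematically between study groups" therefore sits uneasily with the trial's own hypothesis.

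Blinded adjudication protects the judgement on cases that are put forward. It does nothing about cases that are detected in one arm and would have gone undetected in the other.

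An excluded patient leaves all three primary outcomes. If that patient was imaged, admitted or operated on, imaging events and costs leave too. Because the rule is permissive, its application may also vary from case to case.

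**Working it through.** **Inputs from the article.** Expected exclusions are 1–3% (2.3.2). Section 2.8 gives imaging of 30% with a 15-point absolute reduction, ICC 0.01, 10 clusters per group, a mean of 20 analysed patients per cluster, and 500 recruited.

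**The plan's own figures.** The total reproduces: 400/(1 − 0.20) = 500, or 250 per arm. The 1–3% comes from a cited source and cannot be derived from the article. It means 5 to 15 patients overall, or 2.5 to 7.5 per arm. The stated imaging power of 81.99% does not follow from these inputs: standard two-proportion methods give roughly 85% to 92%, depending on the test and continuity correction. That is a separate matter and does not enter the calculation below.

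**Assumptions.** Let π be the prevalence of pathology, with 1–3% used as its range, and q the share in an arm that is confirmed and excluded. Assume everyone excluded had been imaged. With true imaging rate R, the rate after exclusion is (R − πq)/(1 − πq). The values of q are assumptions, because the article gives none.

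| π | q control / PRIME | Control | PRIME | Difference (points) | Change from 15.0 |
|---|---|---|---|---|---|
| 1% | 1 / 0.5 | 0.29/0.99 = 29.3% | 0.145/0.995 = 14.6% | 14.7 | −0.3 |
| 3% | 1 / 0.5 | 0.27/0.97 = 27.8% | 0.135/0.985 = 13.7% | 14.1 | −0.9 |
| 3% | 1 / 1 | 27.8% | 0.12/0.97 = 12.4% | 15.5 | +0.5 |
| 3% | 0.5 / 1 | 0.285/0.985 = 28.9% | 12.4% | 16.6 | +1.6 |
| 3% | 1 / 0 (extreme) | 27.8% | 15.0% | 12.8 | −2.2 |

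Differences are taken before rounding. The third row involves no unequal detection: the shift arises because the analysed population has changed. The fourth row is the mirror case, in which PRIME confirms more. If PRIME had no effect on imaging (30% in both arms), π = 3% with q of 1 and 0.5 would give 27.8% − 28.9% = −1.1 points, an artefact against PRIME.

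**Scale.** Design effect: 1 + 19 × 0.01 = 1.19. Effective size: 200/1.19 = 168.1 per arm. Standard error: √[(0.30 × 0.70 + 0.15 × 0.85)/168.1] = 0.045, or 4.5 points. Shifts of 0.3 to 0.9 points are about 0.1 to 0.2 standard errors, and the extreme row is about 0.5.

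**Costs.** To first order, the mean cost difference shifts by π × (q control − q PRIME) × excess cost per case. The article gives no such cost, so take CHF 5,000 to 50,000 as an assumed range, with q of 1 and 0.5:
- 1%: 0.01 × 0.5 × 5,000 = CHF 25, up to 0.01 × 0.5 × 50,000 = CHF 250 per patient.
- 3%: 0.03 × 0.5 × 5,000 = CHF 75, up to 0.03 × 0.5 × 50,000 = CHF 750 per patient.

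In this direction control loses more expensive patients, so the shift again runs against PRIME. It reverses if PRIME confirms more.

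**The case against.** The best defence is that the exclusion only applies an eligibility criterion to patients whose ineligibility could not be seen at the first visit. It is declared openly, expected in few patients, decided blind and counted in the flow diagram. PRIME aims to cut low-value imaging, not indicated imaging, and it trains GPs to rule out serious causes at the outset, so detection might be equal or earlier under PRIME. The intention-to-treat sentence names practitioner- and patient-level outcomes, not costs. How the discretion is exercised may be set out in the full protocol or analysis plan.

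Much of this stands. It shows that the direction is not fixed and that the imaging effect is small. It does not show that detection is independent of allocation, and an uncertain direction is no reason to condition on the diagnosis. The remark about causes not recognisable at the first visit suggests that the rule is meant for pathology already present, but the article does not make that a limit.

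A reader might infer three stronger things, none of which the document supports:
- That confirmation requires imaging. The article does not say so, and it also lists blood tests and specialist visits.
- That the rule certainly biases the trial in favour of PRIME. If PRIME confirms fewer cases, the shift in imaging and costs runs against PRIME.
- That the rule conceals the main harm of reduced imaging. A diagnosis that is never confirmed does not trigger exclusion, so that patient stays in the analysis. Confirmed exclusions are counted, serious adverse events are monitored (2.6), and the article nowhere calls delayed diagnosis the main harm. What is true is narrower: the flow diagram gives counts, not time to diagnosis, and delayed diagnosis is not a named safety outcome.

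**Conclusion.** The point holds as a selection risk and an inconsistency with the intention-to-treat statements, not as a demonstrated bias. For imaging, confirmation half as frequent under PRIME costs about 0.3 to 0.9 points of a planned 15, and equal confirmation at 3% adds about 0.5. Both are small beside a standard error of about 4.5. These figures rest on assumed confirmation shares and on all excluded patients having been imaged. The cost effect could matter more, because a few expensive cases can move a mean, but CHF 25 to 750 per patient reflects only an assumed cost range. The case for change is that the selection is avoidable and touches all three primary outcomes. It is a worthwhile, inexpensive improvement and not a threat to the trial as a whole.

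**What to change.** - Keep every enrolled patient in the primary intention-to-treat analysis of imaging, RMDQ and cost-effectiveness, by cluster allocation at enrolment, and keep collecting their follow-up data after a diagnosis.
- Use exclusion of confirmed specific pathology only as a sensitivity analysis, limited to pathology that a blinded doctor judges to have been present at the index visit. Replace the permissive wording with a definite rule.
- Report confirmed specific pathology, and time from index consultation to diagnosis, by arm.
- Remove the statement that exclusions are not expected to differ between groups, or present it as an assumption to be examined.

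The cost is a change of wording, continued questionnaires for about 5 to 15 patients, and slight extra noise from the 1–3% of patients retained.

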### Recruitment procedures

2.4

#### Healthcare professionals

2.4.1

Quality circles will be recruited from the Réseau Delta in French-speaking Switzerland (Fig. 1). Eligible quality circles will be identified and contacted through the network coordination team. Quality circles in which at least three GPs agree to participate will be included prior to randomization, ensuring that GPs and the research team remain blinded to group allocation during recruitment. Small quality circles (≤4 GPs) will be merged with another geographically proximate quality circle before randomization to form a single cluster. Additional GPs may be added to randomized clusters if they provide consent after randomization. GPs will provide written informed consent at the start of the pre-study session.

